## Abstract

**Background:**

Prophylactic cranial irradiation (PCI) is the standard preventive strategy for limited-stage small-cell lung cancer (LS-SCLC). However, the evidence supporting this strategy is largely based on the pre-MRI era. With the advancement of modern MRI and treatment techniques, the survival benefit of PCI remains unclear, particularly given the potential for neurocognitive toxicity to impair quality of life. This study aims to re-evaluate the value of PCI in contemporary LS-SCLC patients and investigate whether active MRI surveillance is non-inferior to PCI regarding overall survival (OS).

**Methods:**

This is a prospective, randomized, multicenter, phase III trial, enrolling patients with LS-SCLC who achieve complete response (CR) or partial response (PR) after platinum-based chemoradiotherapy. Participants will be randomly assigned (1:1) to receive either PCI or active MRI surveillance. The primary endpoint is OS. Secondary endpoints include 1- and 3-year OS rates, progression-free survival (PFS), brain metastasis rate, and neurocognitive function. Exploratory analyses will integrate clinical characteristics with the longitudinal kinetics of tumor biomarkers in collected peripheral blood to identify patient subgroups who are more likely to benefit from PCI.

**Discussion:**

This study will re-evaluate the role of PCI in the MRI era for LS-SCLC. If active MRI surveillance proves non-inferior, it may provide evidence supporting a less intensive management approach that could potentially reduce treatment-related neurotoxicity and preserve quality of life. Furthermore, our trial aims to identify patient subgroups that derive a clinical benefit from PCI, and leverage serial biomarker dynamics to guide personalized clinical management for LS-SCLC patients.

**Trial registration:**

This trial is registered at ClinicalTrials.gov (NCT04829708).

## Introduction

Small-cell lung cancer (SCLC) is an aggressive malignancy with a high propensity for early dissemination, particularly to the brain [1, 2]. The brain metastasis rate at one year can be as high as 28% [3, 4]. For decades, PCI has been recommended for patients with LS-SCLC who respond to first-line chemoradiotherapy, based on a meta-analysis which demonstrated a 5.4% increase in 3-year survival and a significant reduction in brain metastasis incidence [5]. However, the trials included in this meta-analysis were conducted prior to the routine use of MRI for staging and follow-up. The question of whether the PCI examined in this study is truly prophylactic or is actually early treatment for potential asymptomatic brain metastases was extensively discussed.

The evolution of MRI technology has significantly increased the detection rate of intracranial metastases, enabling the identification of subclinical lesions before symptoms occur. A retrospective analysis of LS-SCLC patients indicates that PCI provided no significant benefit over observation regarding 3-year brain metastasis incidence (20.4% vs. 11.2%, *p* = 0.10) or overall survival (*p* = 0.32) [6]. Similarly, another meta-analysis indicated that among patients confirmed free of brain metastases via MRI, PCI conferred no significant overall survival benefit (HR 0.74; 95% CI, 0.52–1.05; *p* = 0.08; *n* = 9 studies; *n* = 1384 patients) [7]. Therefore, the strategy of early intervention for MRI-detected lesions warrants investigation as a potential alternative to PCI in LS-SCLC. Notably, a prospective Japanese trial in ES-SCLC found that PCI offered no survival advantage and was associated with neurocognitive toxicity [8]. Given the lack of randomized controlled data for LS-SCLC, there is a pressing need for prospective research to assess the efficacy and safety of PCI in the era of advanced MRI.

The advent of high-resolution MRI allows for the early detection of limited brain metastases, while advances in stereotactic radiation (SRS/SRT) offer a highly effective and focal treatment option [9–13]. A retrospective study comparing SRS and whole brain radiotherapy (WBRT) in SCLC patients with limited brain metastases revealed no significant difference in prognosis [9]. Furthermore, multiple studies have demonstrated that SRS is associated with significantly lower neurotoxicity compared to PCI and WBRT [10–14]. The integration of MRI and SRS/SRT creates new opportunities for early detection and management of brain metastases in LS-SCLC, potentially preserving both treatment efficacy and quality of life, suggesting that PCI may no longer be an obligatory choice.

Consequently, we launched a randomized, multicenter, phase III study (NCT04829708) to establish prospective evidence comparing the efficacy and safety of PCI against MRI surveillance in LS-SCLC patients with confirmed response to first-line chemoradiotherapy. This study will also assess the long-term neurocognitive effects of PCI and determine if modern hippocampal-sparing techniques offer improved safety and survival outcomes. Additionally, by integrating clinical characteristics with serial analyses of peripheral blood biomarkers, we aim to screen for populations that benefit from PCI, thereby facilitating personalized clinical management.

## Methods

### Study design and setting

This is a prospective, open-label, randomized controlled, multicenter, phase III clinical trial designed to evaluate the efficacy and safety of PCI compared with cranial MRI surveillance in patients with LS-SCLC who have achieved a response (CR or PR) following first-line chemoradiotherapy. The study will be conducted across multiple tertiary hospitals in China with expertise in thoracic oncology, radiation oncology, and neurocognitive assessment.

Eligible participants will be randomized in a 1:1 ratio to either the PCI arm or the MRI surveillance arm. Randomization will be stratified according to response status (CR vs. PR), tumor stage (I/II vs. III), and radiotherapy schedule (concurrent vs. sequential). Study coordination, data collection, and management will be centrally overseen by the sponsor; routine monitoring will ensure data quality and adherence to the protocol. The trial is conducted in accordance with Good Clinical Practice and the Declaration of Helsinki, with written informed consent obtained for all patients. This trial is registered at ClinicalTrials.gov (NCT04829708). Any significant protocol modifications, including changes to eligibility criteria, study endpoints, or statistical analyses, will be submitted to the IRB and updated in the trial registry as required. Protocol version 1.3, finalized in September 2024, was used for this submission.

### Participants

#### Key eligibility criteria

Patients will be eligible for enrollment if they meet all of the following criteria:

(I)Provision of written informed consent;(II)Age ≥ 18 years and ≤ 75 years at the time of enrollment;(III)Histologically or cytologically confirmed LS-SCLC (according to the VALG staging system);(IV)Completion of first-line chemoradiotherapy with radiologically confirmed CR or PR according to RECIST v1.1 [15]; patients who have received immunotherapy as part of first-line treatment are also eligible.(V)No evidence of brain or meningeal metastases on brain MRI performed within 4 weeks prior to enrollment;(V1)ECOG performance status of 0 to 2 [16], with no deterioration in the preceding 2 weeks;(VII)Interval between completion of the last treatment cycle and randomization not exceeding 8 weeks;(VIII)Life expectancy of ≥ 12 weeks;(IX)Adequate organ function, defined as absolute neutrophil count ≥ 1.5 × 10⁹/L, platelets ≥ 75 × 10⁹/L, hemoglobin ≥ 9.0 g/dL, normal coagulation function, and adequate hepatic and renal function.

#### Key exclusion criteria are as follows:

(I)Diagnosis of extensive-stage SCLC (ES-SCLC) or combined SCLC;(II)Confirmed brain or meningeal metastases prior to randomization;(III)History of other active malignancies within 5 years (excluding curable non-melanoma skin cancer or in situ carcinomas);(IV)Prior head and neck radiotherapy with field overlap precluding PCI;(V)Contraindications to MRI or severe, uncontrolled comorbidities (e.g., severe cardiovascular disease, recent stroke within 6 months);(VI)Pregnant or breastfeeding women.(VII)Any other condition meeting the general exclusion criteria, including but not limited to severe hematologic, cardiac, hepatic, or renal dysfunction or immunodeficiency.

### Overall study design

Before enrollment, all patients must have completed at least two cycles of chemotherapy and definitive radiotherapy, achieving a confirmed radiological response (CR or PR). The prescribed planning target volume (PTV) radiation dose is 54–66 Gy delivered in 1.8–2.0 Gy once-daily fractions or 45 Gy delivered in 1.5 Gy twice-daily fractions. Baseline imaging, including contrast-enhanced chest and abdominal computed tomography (CT) or positron emission tomography–computed tomography (PET-CT), and brain MRI, will be performed within 4 weeks prior to enrollment to exclude intracranial metastases.Bone scintigraphy is recommended for patients with clinical suspicion of bone metastases.

Eligible patients will undergo randomization within 8 weeks after completion of first-line chemoradiotherapy. Patients assigned to the PCI group will undergo prophylactic whole-brain radiotherapy within 8 weeks after the completion of CRT. The prescribed total dose is 25 Gy delivered in 10 fractions (2.5 Gy per fraction), administered once daily, 5 days per week. Hippocampal avoidance (HA) techniques are recommended to minimize neurocognitive toxicity.

Patients assigned to the MRI surveillance group will undergo active surveillance. Follow-up assessments for both groups will include cranial MRI every no more than 3 months for the first 24 months, and every no more than 6 months thereafter until the detection of brain metastases. Imaging should be performed immediately when symptoms arise, including headache, dizziness, diplopia, nausea, or vomiting. Additionally, contrast-enhanced CT of the neck, chest, and abdomen is recommended, where feasible, to identify any extracranial disease progression or recurrence. For patients who develop brain metastases, subsequent local therapy (such as WBRT or SRS) will be determined by the treating investigator based on the number and size of metastases, patient performance status, and institutional guidelines. Following completion of salvage treatment, patients will undergo surveillance with contrast-enhanced MRI or CT every 2–3 months for the first 24 months, and every 6 months thereafter until the development of subsequent intracranial metastases. A schematic of the study process is shown in Fig. 1.

**Fig. 1 Fig1:**
[figure not shown]
Flowchart of the study. CRT, chemoradiotherapy; CR, complete response; PR, partial response; MMSE, Mini-Mental State Examination

Both groups will undergo identical schedules for systemic disease evaluation. Follow-up visits will include clinical assessment, toxicity evaluation, imaging, and peripheral blood monitoring as per institutional standards, as well as neurocognitive function assessment. All patients will be followed for survival until death, withdrawal of consent, or study closure.

### Neurocognitive function assessment

To evaluate the potential neurotoxicity associated with PCI compared to surveillance, neurocognitive function will be assessed at pre-specified time points: baseline, and at 3, 6, 12, and 24 months after randomization. Assessments will be performed using the Mini-Mental State Examination (MMSE) scale [17] and a standardized neurological examination checklist [18]. Results will be correlated with quality of life (QoL) outcomes [19].

### Dynamic peripheral blood monitoring

In this trial, peripheral blood is harvested periodically: at baseline, periodically during the follow-up period, and additionally upon disease progression. Tumor marker assessments are performed at every follow-up visit. Follow-up persists until death or withdrawal. By dynamically monitoring inflammatory indices and tumor markers, integrating these longitudinal changes with clinical characteristics, we will employ machine learning models to identify patient subgroups that derive survival benefits from PCI. This approach provides new insights for precision prophylactic strategies against brain metastases in LS-SCLC.

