### Endpoints

The primary endpoint is OS, defined as the time from randomization to death from any cause or lost to follow-up. Secondary endpoints include the 1-year and 3-year OS rates, PFS, intracranial metastasis rate, and neurocognitive function changes assessed by MMSE at specified intervals. Progression-free survival (PFS) will be assessed by investigators according to the Response Evaluation Criteria in Solid Tumors (RECIST) version 1.1 criteria, without blinded independent central review. Validated patient-reported outcome measures will be used to assess QoL where feasible. Exploratory analyses will aim to identify specific patient subgroups that derive the benefit from PCI based on clinical characteristics and longitudinal dynamic biomarkers.

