The advent of immunotherapy has further reshaped the treatment landscape of LS-SCLC, with durvalumab consolidation following chemoradiotherapy now established as the new standard of care. The ADRIATIC trial results indicated that while durvalumab was effective whether or not patients undergo PCI, those receiving PCI showed slightly higher 3-year OS rate: 62.1% in the PCI group compared to 50.2% in the non-PCI group (HR 0.75). Grade 3–4 adverse events occurred in 28.4% of the PCI group versus 19.8% in the non-PCI group(19,28). These findings necessitate a reassessment of the utility of PCI within current immunotherapy treatment landscapes. Our randomized study includes patients who have received first-line immunotherapy, particularly those receiving consolidation immunotherapy, aiming to reassess the role of PCI in the modern treatment era and identify patients who may derive benefit from prophylactic irradiation.

Although our trial has been carefully designed, several limitations should be acknowledged. First, this is an open-label study, as blinding of treatment assignment is not feasible given the inherent characteristics of radiotherapy. Second, the choice of local treatment after the detection of brain metastases in the surveillance arm (e.g., WBRT vs. SRS) was decided jointly by patients and investigators, which may introduce heterogeneity in subsequent patient management and clinical outcomes. To minimize its impact, all post-progression treatments will be systematically documented, and prespecified subgroup analyses will be performed. Third, although MMSE was selected because of its simplicity, feasibility, and widespread use in routine clinical practice and previous PCI-related studies, it may have limited sensitivity for detecting subtle cognitive impairment associated with PCI, particularly in executive function, attention, and delayed recall. More sensitive assessment tools such as the Montreal Cognitive Assessment (MoCA), may provide a more detailed evaluation of PCI-related neurotoxicity and should be incorporated into future prospective studies. Finally, the prolonged follow-up required for overall survival assessment may increase the risk of patient attrition. To mitigate this, we will implement centralized data management and active patient engagement strategies to ensure data integrity and follow-up compliance.

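### The exploratory search for patients who benefit from PCI uses marker changes measured after randomisation, so the PCI effects it reports within subgroups can be false

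*Protocol article*

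**What the plan says.** Blood is taken "at baseline, periodically during the follow-up period, and additionally upon disease progression" (Dynamic peripheral blood monitoring). The same section states the use: "integrating these longitudinal changes with clinical characteristics, we will employ machine learning models to identify patient subgroups that derive survival benefits from PCI". The Endpoints section repeats the aim and labels it exploratory: "Exploratory analyses will aim to identify specific patient subgroups that derive the benefit from PCI based on clinical characteristics and longitudinal dynamic biomarkers". OS runs from randomisation (Endpoints), and the method named for OS subgroups is the Cox model (Statistical analysis). PCI is to be given within 8 weeks of completing chemoradiotherapy (Overall study design).

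Two further statements are related:

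- **Salvage treatment.** Local therapy after brain metastasis "will be determined by the treating investigator based on the number and size of metastases, patient performance status, and institutional guidelines" (Overall study design). The Discussion answers the resulting heterogeneity by saying that "all post-progression treatments will be systematically documented, and prespecified subgroup analyses will be performed". It does not name the grouping variable.
- **Hippocampal avoidance.** The Introduction says the study will "determine if modern hippocampal-sparing techniques offer improved safety and survival outcomes". In Overall study design, "Hippocampal avoidance (HA) techniques are recommended to minimize neurocognitive toxicity". It is not randomised and is not among the stratification factors, which are response, stage and radiotherapy schedule.

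**The concern.** A subgroup can show who benefits from a treatment only if membership is settled before the treatment can influence it. Marker paths during follow-up fail this in three ways.

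1. **PCI can change membership.** If PCI prevents brain metastases, it can alter markers that respond to progression. Patients with a stable marker are then a different selection in each arm, and randomisation no longer protects their comparison.
2. **Membership depends on survival.** A patient must live long enough to show a rise. Classifying by the rise but counting survival from randomisation gives that group immortal time.
3. **The information comes too late.** A path observed over later visits does not exist when PCI is decided, so it cannot select patients for PCI, even if it is strongly prognostic.

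Finding who benefits is presented as an aim in the abstract, the Introduction and the Discussion. A false subgroup effect would bear on who is thought to need irradiation.

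**Working it through.** **The plan's own figures.** The article gives no figure for this analysis. Its primary sizing is separate and reproduces: with the assumed hazard ratio 22/23.5 rounded to 0.94, events = 4 × (1.960 + 0.842)² / [ln(1.25/0.94)]² = 31.4 / 0.0812 = 387, as stated. Nothing below changes it.

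**Illustration: inputs.**

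- From the article: median OS 22 months, used here in both arms so that PCI has no OS effect; brain-metastasis rate up to 28% at one year (Introduction), taken here as the rate without PCI; accrual 60 months plus 20 months of follow-up, so administrative censoring at 20 to 80 months.
- Assumed: PCI halves the brain-metastasis hazard. Grouping is by whether brain metastasis occurs before death or censoring. This stands in for a post-randomisation variable; no marker is modelled.

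**Hazards per month.** Death: λ = ln 2 / 22 = 0.0315. Brain metastasis: μ = −ln(0.72)/12 = 0.0274 under surveillance and 0.0137 under PCI.

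**Why the comparison goes wrong.** Take independent risks and no censoring. A patient counts as event-free only by dying before a metastasis appears, and the time to death given that has hazard λ + μ. The surveillance-versus-PCI ratio among event-free patients is (0.0315 + 0.0274)/(0.0315 + 0.0137) = 0.0589/0.0452 = 1.30, although the true effect is 1.00. Censoring at 20 to 80 months dilutes this, as the simulation shows.

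**Simulated surveillance-versus-PCI hazard ratios** (Cox model, true effect 1.00; a shared frailty multiplies both hazards):

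| Shared risk of metastasis and death | All patients | Later metastasis | Event-free |
|---|---|---|---|
| None (independent) | 1.00 | 1.10 | 1.24 |
| Frailty variance 0.3 | 1.00 | – | 1.14 |
| Frailty variance 1.0 | 1.00 | 1.01 | 1.03 |

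**At the trial's size.** A second simulation used 544 patients and 400 runs per setting, with no PCI effect on OS, a log-normal frailty (SD 0.8 on the log hazard), and the brain-metastasis hazard multiplied by 0.5 or 0.3 under PCI. Ratios here are PCI versus surveillance, so values below 1 favour PCI.

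| Grouping variable | PCI ratio in the event-free or low-marker group | Nominal 5% rejections in that group |
|---|---|---|
| Any later progression | 0.92 / 0.87 | 15% / 20% |
| Later brain metastasis | 0.91 / 0.86 | 15% / 26% |
| Baseline marker | 1.00 / 1.00 | 4.5% / 5.5% |

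Patients with the later event had a ratio for death of 0.53 to 0.58 against event-free patients, although their underlying risk was higher. That is immortal time.

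**Limits of the illustration.** The treatment-by-group interaction test stayed near its nominal level in these settings (4.8% to 7.5%), so the distortion lies mainly in the within-group PCI effect. In another setting, grouping by progression within the first 12 months gave ratios of 0.99 and 1.01. The bias is therefore possible, not inevitable, and its size depends on how the groups are formed.

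**The case against.** **The analysis is exploratory and the analysis plan is not shown.** Both are true, and how later values enter a model is properly left to that plan. Baseline blood and clinical characteristics are also inputs, and landmark, time-dependent or joint models can handle later values. So it would be too strong to say that the analysis cannot be informative or will produce false benefit. What stands is the purpose that the article itself assigns to the longitudinal changes. Better modelling can make them sound for prognosis but cannot make them available when PCI is decided.

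**Stronger readings that the article does not support:**

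- *Three planned analyses share this fault.* A reader might infer this, but only the marker analysis is set out in Methods. The Discussion never names its subgroup variable. Grouping by salvage treatment received is the natural reading, but it is an inference.
- *Hippocampal avoidance is another flawed test of who benefits from PCI.* It is a comparison of techniques within the PCI arm. Its weakness is confounding, not conditioning on a later outcome. The article does not say who chooses the technique.
- *The bias is as large as the non-inferiority margin.* The 1.24 is the extreme case of independent risks, and the 1.25 margin belongs to the primary test only. The comparison carries no meaning.

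**Conclusion.** The point holds for the marker analysis. As stated, it would use variables that treatment and survival can both influence to identify who benefits from that treatment, and within-subgroup PCI effects on OS can be false as a result. In the illustration, the false surveillance-versus-PCI ratio among event-free patients runs from 1.03 to 1.24 against 1.00 overall. That range rests on an assumed halving of the brain-metastasis hazard, no PCI effect on OS, and brain metastasis standing in for a marker. It shows the mechanism and does not forecast this trial's result.

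The Discussion's subgroups share the fault only if they are defined by treatment received. For hippocampal avoidance, the point is one of wording: a technique that is recommended and not randomised does not let the trial establish its effect on safety or survival. The matter should be corrected, but the primary OS comparison, its 387 events and its 544 patients stand.

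**What to change.** - **PCI-benefit models.** Restrict models and subgroup tests of PCI benefit to variables fixed at randomisation (baseline markers and clinical factors), and judge them by treatment-by-factor interaction.
- **Later kinetics.** Use them for prognosis only, by landmark, time-dependent or joint models, and say so.
- **Post-progression treatment.** Name the subgroup variable meant in the Discussion. If it is treatment received, report that treatment descriptively by arm and do not compare OS between arms within those groups.
- **Hippocampal avoidance.** Reword the Introduction's aim as an observational, descriptive comparison within the PCI arm.

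The cost is wording in the protocol and analysis plan, with no change to sample size or visits. The downside is a narrower exploratory claim: follow-up kinetics could describe outlook but not select patients for PCI.
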